### Who will take informed consent? {26a}

Local principal investigators, sub-investigators, trained research nurses, or residents will introduce the trial to the patients or to their legal representatives in case the patients are unable to understand due to communicative or cognitive limitations. The same operators will obtain written consent before randomization from all eligible patients or their legal representatives. Informed consent will be collected according to current national regulations. If patients with legal representatives regain their ability to consent, a second written consent will be requested. In circumstances where patients are unable to consent due to the nature of the underlying disease process (e.g., hypercapnic ARF) or treatments (e.g., sedative medications, mechanical ventilation), in the absence of a legal representative, patients will be randomized, and written consent will be obtained once patients regain their ability to consent. If patients understand and consent to the study, but they are not able to sign a written consent, they will be allowed to verbally agree in the presence of a witness. This verbal consent will then be documented in the medical records. Once the clinical situation improves, the patient will be asked to sign the consent form before being discharged. If a patient dies before a written informed consent can be obtained, his/her data may also potentially be used.

At any time during the clinical study, patients can freely withdraw their informed consent. In this case, no further data will be collected, and the data already collected will be deleted. Participants who abandon the study will be replaced with the aim of reaching the number of subjects envisaged by the sample size, with the possible need to extend the inclusion period.

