### Sample size {14}

Given a type I error of 0.05, a power of 0.8, an expected proportion of patients who develop pressure sores in the control group of 23% [39], and an expected dropout rate of 5%, 239 subjects per group are estimated to identify a 10% absolute difference in the proportion of patients developing pressure sores between intervention and control groups measured at 36 h from randomization.

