## Assignment of interventions: blinding

### Who will be blinded {17a}

Due to the nature of the intervention tested, trial participants and care providers will not be blinded after being assigned to an intervention. However, assessors and data analysts will not participate in the care of the patient and will be blinded to patient group assignment.

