## Statistical methods

### Statistical methods for primary and secondary outcomes {20a}

The analysis will be performed according to the intention-to-treat (ITT) principle. Descriptive statistics will be calculated to summarize patient characteristics collected at study entry according to the randomization group. Categorical variables will be reported as absolute frequencies and percentages. Continuous variables will be represented as mean and standard deviation or median first and third quartiles if not normally distributed according to the Shapiro–Wilk test.

The raw risk of pressure sore will be calculated at each time point as the ratio between the number of subjects who developed a pressure sore at a given time point divided by the number of subjects undergoing NIV at that time point. Patients having a planned break at the time point considered, but not weaned off NIV, will be considered as patients undergoing NIV.

Mixed effect logistic regression models will be used to estimate the risk of pressure sores and the difference between interfaces, including a random intercept to account for clustering of the subjects within the center and repeated measures within patients. The response variable will be the presence/absence of pressure sores, whereas the independent variables will be the treatment, time (12, 24, 36, 48, 60, 72, 84, 96 h), and their interaction. The marginal predicted probabilities estimated by the model will provide the incidence of pressure sores at different times as well as overall. The inclusion of time as a covariate will allow to test the presence of a time trend in the incidence of pressure sores and to investigate the variation of time trends according to treatment group.

If the descriptive statistics will detect unbalanced characteristics between randomization groups (e.g., indication for NIV), the corresponding variables will be added as covariates in the logistic regression model.

Regarding the number of pressure sores, different mixed effect Poisson regression models will be applied: one for each time point to estimate the average number of pressure sores at each time point and a model in which only the highest number of pressure sores will be considered for each patient. Time will be included as offset to evaluate the average number of pressure sores per day.

The grade and location of pressure sores will be summarized using descriptive statistics at each time point.

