### Methods in analysis to handle protocol non-adherence and any statistical methods to handle missing data {20c}

Protocol non-adherence will be handled by performing the analyses according to the ITT principle, specifically, patients will be analyzed considering their allocation group regardless of the intervention they will follow. Moreover, deviation from the protocol will be registered as well as the reason for deviation. The missing rate is expected to be very low, therefore no specific analyses to handle missing data are planned. However, if needed (i.e., missing rate between 20 and 40%) multiple imputation through expectation–maximization algorithm will be applied and the results obtained from analysis of the new data will be considered as sensitivity analysis.

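### Deleting the data of patients who withdraw consent, and replacing those who leave, contradicts the declared intention-to-treat analysis in an open-label trial where some consent is sought after randomisation

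*Protocol article*

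**What the plan says.** All references are to the protocol article.

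- **Who will take informed consent? {26a}.** After withdrawal of consent, "no further data will be collected, and the data already collected will be deleted". The same paragraph adds: "Participants who abandon the study will be replaced with the aim of reaching the number of subjects envisaged by the sample size". The article does not say whether leaving the study in this sense is wider than withdrawing consent.
- **Same section, consent after randomisation.** If a patient cannot consent and has no legal representative, "patients will be randomized, and written consent will be obtained once patients regain their ability to consent". Where a representative consented first: "If patients with legal representatives regain their ability to consent, a second written consent will be requested".
- **Who will be blinded {17a}.** "trial participants and care providers will not be blinded after being assigned to an intervention".
- **Statistical methods {20a}.** "The analysis will be performed according to the intention-to-treat (ITT) principle". Section {20c} explains this as analysing patients in their allocated group whatever intervention they follow.
- **Sample size {14}.** 239 per group, for 23% in the control group and a 10-point absolute difference, with "an expected dropout rate of 5" percent already in the figure.

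**The concern.** An intention-to-treat comparison rests on every randomised patient being counted in the allocated arm. A patient whose record has been erased cannot be counted in any arm, and no later analysis plan can bring the record back. The two rules therefore contradict each other, and the article does not define the analysis set that results.

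This matters because withdrawal here need not be random. Patients know their arm, and mask burden differs by design: a change every 6 h in one arm, a change only for discomfort or a sore in the other. A patient asked for first or second consent after randomisation may already have worn the masks and may already have a sore. The article itself links sores to discomfort, intolerance and stopping NIV (Abstract, Discussion; Background {6a}). If those who leave have a different sore risk, and leave at different rates by arm, the patients who remain are no longer comparable.

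Replacement does not repair this. A new patient adds to the count but does not stand in for the one removed. Because allocation is by independent draws with probability 0.5 ({16a}), the replacement need not even enter the same arm. Deletion also removes tolerability information, since section {22} reports minor adverse events through the study outcomes.

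**Working it through.** **1. The plan's sample size.** Inputs from {14}: 23% vs 13% (the 10-point difference taken as a reduction), alpha 0.05, power 0.80. A two-sided test is assumed, since {14} does not state the sidedness.

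- Unpooled normal formula: n = (1.960 + 0.842)² × (0.23×0.77 + 0.13×0.87) / 0.10² = 7.849 × 0.2902 / 0.01 = 227.8, so 228 per arm.
- With 5% dropout: 227.8 × 1.05 = 239.2, or 227.8 / 0.95 = 239.8.

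The stated 239 is reproduced to within rounding, so it already contains the 5%.

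**2. What replacement adds at the planned 5% loss.** The replacement target is read as 239, the only number {14} gives.

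| | Randomised per arm | Analysed per arm | Power, 23% vs 13% |
|---|---|---|---|
| No replacement | 239 | 239 × 0.95 = 227 | 79.4% |
| Replace until 239 are retained | 239 / 0.95 = 252 | 239 | 81.4% |

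The power figures use the pooled-variance test. Replacement costs 252 − 239 = 13 more patients per arm (504 against 478 in total) and raises power slightly.

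**3. Illustration of the bias.** Let p be the true 36 h risk, w the fraction of an arm withdrawn and erased, and q the sore risk among those erased. The risk seen in the remaining patients is (p − wq)/(1 − w). Take p = 0.23 in both arms, so there is no true effect. Assume q = 0.50; the documents give neither q nor w.

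| w | Calculation | Observed risk |
|---|---|---|
| 2% | (0.23 − 0.010)/0.98 | 22.4% |
| 3% | (0.23 − 0.015)/0.97 | 22.2% |
| 7% | (0.23 − 0.035)/0.93 | 21.0% |
| 8% | (0.23 − 0.040)/0.92 | 20.7% |
| 10% | (0.23 − 0.050)/0.90 | 20.0% |

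Spurious differences between arms:

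- 3% vs 7%: 1.2 points.
- 3% vs 8%: 1.5 points.
- 2% vs 10%: 2.4 points.

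With q above p, the arm that loses more patients looks better, whichever arm that is. With q = p there is no bias. With the same w and the same q in both arms there is also none.

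For scale, the standard error of the difference at 239 per arm is √(2 × 0.23 × 0.77 / 239) = 0.0385, or 3.85 points. The 3% vs 7% case is thus about 1.2 / 3.85 = 0.3 standard errors.

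**The case against.** The strongest reply is that the effect is likely to be small and the deletion rule may not be the sponsor's to choose.

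- **Size.** Section {18b} expects negligible loss over a short follow-up. Two of the three scenarios above average more than the whole 5% allowance (5.5% and 6%), and the 50% sore risk is assumed. This stands: the figures are illustrative.
- **Existing outlets.** A patient who finds a mask unbearable can continue with the other mask or change interface ({11a}), and non-adherent patients stay in their allocated group ({20c}). This should reduce withdrawals of consent, but it does not change what happens to those who do withdraw.
- **Consent law.** Consent follows national regulations, and whether these require deletion cannot be checked from the article. If they do, the analysis still has to be described for what it is.

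A reader might also infer more than the text supports:

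- **That refusing deferred or second consent triggers deletion.** The sentence covers withdrawal of consent; the article does not say what happens on such a refusal. Randomisation before any consent is also limited to patients who cannot consent and have no representative.
- **That the double allowance for dropout harms the trial.** It costs patients, not power. Dropout is not defined in {14} and may cover other losses.
- **That erased patients cannot even be counted.** Allocation is held in REDCap, and the coordinating centre reviews reports on inclusion and follow-up ({19}), so counts by arm may survive.
- **That the imputation trigger ("missing rate between 20 and 40" percent, {20c}) is part of this fault.** It is a separate matter, of a kind often settled in an analysis plan.

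**Conclusion.** The contradiction stands on the text alone: the rule that erases data on withdrawal, and the rule that replaces those who leave, do not fit the declared intention-to-treat analysis. The analysed set would be those who stayed. Open-label treatment and consent sought after randomisation make it plausible that staying depends on arm and outcome.

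The size of the bias cannot be derived from the documents. The illustrations, roughly 1.2 to 2.4 points against a 10-point target, rest on assumed withdrawal rates and an assumed 50% sore risk among those who withdraw. They do not show a bias in favour of rotation: the sign depends on which arm loses more, and there is none if withdrawal is unrelated to sores.

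The sample-size point is secondary. Since 239 already includes the 5%, replacement is unnecessary at the planned loss: about 227 analysed per arm gives 79.4% power. That is inefficiency only.

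**What to change.** Amend the consent and analysis wording for patients consented after the amendment, as far as consent rules allow:

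1. Separate stopping the assigned strategy from withdrawing consent for the use of data.
2. Keep data collected up to withdrawal unless the patient explicitly asks for erasure.
3. State what happens to data when deferred or second consent is refused.
4. Do not replace randomised patients; rely on the 5% already in the 239.
5. Analyse all randomised patients with retained data by allocated arm, and report withdrawals and erasures by arm.
6. Add a best-case/worst-case sensitivity analysis for erased or missing 36 h outcomes. For erased patients this needs only the counts by arm.

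If erasure must stay, do not call the analysis set full intention-to-treat.

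The cost is an ethics-approved wording change. Section {25} requires approval at each participating centre, and 23 centres are planned. Recruitment began in December 2022, so patients already enrolled under the present promise of deletion would keep it. A few patients with partial follow-up would remain in the analysis.

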### Additional consent provisions for collection and use of participant data and biological specimens {26b}

No ancillary studies have been planned so far, and no biological specimens will be collected.

## Interventions

### Explanation for the choice of comparators {6b}

Two groups will be compared. In the control group (i.e., standard-of-care group), interface rotation during NIV will be allowed only in case patients develop pressure ulcer or become intolerant to the interface. In the treatment group, patients will rotate two interfaces, chosen among those used in that center, every 6 h.

### Intervention description {11a}

In the control group, mask will be chosen among the three types of masks available: oronasal, total face, or hybrid mask, according to the standard of care of the participating centers. Patients wearing oronasal masks will receive protective dressing on their nasal bridges before starting NIV. Interface will be changed in case of discomfort, referred by the patient as unbearable, or in the presence of a pressure sore.

In the intervention group, the mask initially applied to the patient will be randomly chosen between the two most used masks in that center among those available (i.e., oronasal, total face, or hybrid mask). Thereafter, NIV mask will be changed every 6 h, alternating the two different interfaces. Patients wearing oronasal masks will receive a protective dressing on the nasal bridge before starting NIV. In case of discomfort, referred by the patient as unbearable related to one of the two interfaces, NIV will be continued with the other mask.

In both arms, the treatment will be continued until patients require NIV according to the assigned protocol.

Prior to patient recruitment, the candidate assessors (doctors and nurses) will be trained to recognize and stage pressure sores through a specific standardized education module. At the end of this course, the trainees will be asked to take a final test where they have to correctly stage 10 pressure sores. Only those trainees able to identify and stage all 10 sores will be qualified as assessors. To minimize detection bias, assessors will not participate in patient care and will be blinded to treatment allocation.

The skin underneath the mask and occipital region will be inspected every 12 h for possible damage by the assessors. If a pressure sore is detected, the physician in charge of the patient will be promptly informed, and a note will be written on the nursing record. Pressure sores will be staged according to the classification of the National Pressure Ulcer Advisory Panel, European Pressure Ulcer Advisory Panel, and Pan Pacific Pressure Injury Alliance [36] (Table 1).

**Table 1 Tab1:** Pressure sores classification according to the classification of the National Pressure Ulcer Advisory Panel, European Pressure Ulcer Advisory Panel, and Pan Pacific Pressure Injury Alliance

Stage I	A reddened, painful area on the skin that does not turn white when pressed. This is a sign that a pressure ulcer may be forming. The skin may be warm, cool, firm, or soft.
Stage II	The skin blisters or forms an open sore. The area around the sore may be red and irritated.
Stage III	The skin now develops an open, sunken hole called a crater. The tissue below the skin is damaged. It is possible to see body fat in the crater.
Stage IV	The pressure ulcer has become so deep that there is damage to the muscle and bone, and sometimes to tendons and joints.
Unstageable	Is not possible to see the bottom of the sore, and it is impossible to establish how deep it is
Suspected deep tissue injury	The surface of the skin looks like a Stage 1 or 2 sore, but underneath the surface, it appears as a Stage III or IV.

Discomfort due to the mask will be evaluated every 12 h using a 5-level Likert-like scale [17, 37] to answer the questions “How is your level of discomfort related to the mask?”. The extremes of the scale are “1—no discomfort” and “5—unbearable discomfort,” with three intermediate levels: “light discomfort,” “moderate discomfort,” and “intense discomfort”).

In both groups, in case of the presence of a new pressure ulcer, the strategy that can be applied comprehend (1) application of a wound care dressing or a different kind of wound care dressing; (2) reduction of the time spent on NIV; and (3) change interface.

### Criteria for discontinuing or modifying allocated interventions {11b}

Patients will discontinue NIV treatments in case of improvement, worsening leading to intubation, or in case of death.

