**Discussion:**

The development of pressure ulcers is a common side effect of NIV that negatively affects the patients’ comfort and tolerance, often leading to NIV failure and adverse outcomes. The ROTA-USE STUDY will determine whether a protocolized rotational approach can reduce the incidence, number, and severity of pressure ulcers in NIV-treated patients.

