## Introduction

### Background and rationale {6a}

In recent years, noninvasive ventilation (NIV) has increasingly become a common approach for the treatment of hypercapnic [1, 2] and hypoxemic [3] patients both inside [3] and outside [4–6] the intensive care unit (ICU). NIV refers to the delivery of a positive pressure to the patient through interfaces like masks or helmets without the need for invasive endotracheal intubation [7]. These interfaces can efficiently and non-invasively support patients with acute respiratory failure (ARF), preserving airway defense mechanisms, speech, and swallowing, averting the need for prolonged sedation, lowering the occurrence of ventilator-associated pneumonia [8], and ultimately reducing ICU admission [9] and mortality [2]. Nonetheless, NIV failure is observed in 8% of hypercapnic [10] and 50% of hypoxemic patients [11], leading to delayed initiation of invasive ventilation treatment and poor outcomes [5, 10, 12, 13].

As patient comfort is a major factor for NIV success [14], the selection of the most suitable interface type is of paramount importance [15]. Another key variable that should be taken into account to achieve patient comfort and avoid the generation of skin breakdown until pressure ulcers, a frequently observed NIV side effect [7], is the time of exposure to a given interface. Indeed, when the pressure applied between the interface and the skin exceeds the capillary pressure, skin breakdown may occur, resulting in NIV discontinuation due to pain and intolerance [16]. Published incidence rates of facial pressure ulcers associated with NIV masks range from 2 to 31% [17–22] depending on the type of mask used, length of treatment, ventilator setting, humidification, nutritional status, and preventative measures adopted.

The development of pressure ulcers is associated with adverse outcomes that may contribute to patient pain and suffering, impaired quality of life [23], and increased hospital costs [24, 25].

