### Outcomes {12}

The primary effectiveness outcome is the proportion of patients developing at least one pressure sore of any stage at 36 h from randomization. The reason why this measure of effectiveness was chosen is that it is more clinically relevant than the overall number of pressure sores. Furthermore, 36 h seems to be an appropriate time point given that the time it takes for pressure sores to develop is extremely variable, but it might as well be very short.

Secondary outcomes will be the onset, number, and stage of pressure sores and comfort during NIV measured at different time points (12, 24, 36, 48, 60, 72, 84, 96 h). At the same time points, the location of pressure sores per patient will also be recorded, i.e., forehead, nose bridge, left cheek, right cheek, chin, left periauricular, right periauricular, and occipital. The study will also monitor the number of patients that interrupts NIV due to discomfort, the presence/absence of eye irritation in relation to both oronasal and full face/hybrid mask, poor adherence to the protocol (e.g., duration of NIV treatment/day, interfaces changed and hygiene protocol application both during each 12-h protocol period) and the presence/absence and types of vasoactive medications, i.e., epinephrine, norepinephrine, vasopressin, dobutamine, dopamine, other. Further outcomes include the costs for intervention implementation (e.g., mask-related costs) and those related to the care of pressure sores (antibiotic treatment, specialist medical visits).

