### Composition of the data monitoring committee, its role and reporting structure {21a}

The data monitoring group is composed by [name] (lead investigator), [name] (lead investigator), and [name] (lead investigator). The role of the data monitoring committee is to independently review the study protocol, recruitment of patients and liaising with the principal investigator to be involved in the safety monitoring interim analysis, and agreement on the final manuscripts. The Data Quality Assurance group is composed by [name], [name], [name], [name], and [name] and will be responsible for monitoring data for inconsistency and missing data.

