### Adverse event reporting and harms {22}

Interfaces for noninvasive ventilation should be considered as a non-significant risk device according to the definition given from the Food and Drug Administration. Besides, the present randomized controlled trial does not intend to investigate a new interface but the protocolized rotational use of commercially available interfaces. As patients with contraindications to NIV/with known hypersensitivity to skin protective devices will be excluded from the study, the potential for serious adverse events related to a protocolized rotation use of interfaces appears remote. Possible minor adverse events consequent to the use of noninvasive ventilation interfaces consist of pressure sores, dryness of the mouth, eye redness, and discomfort. All these information will be recorded and reported as primary and secondary outcomes of the study.

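### Intubation and death take patients out of the on-NIV sore denominator, but neither is an outcome compared by arm and the interim criterion covers sores only

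*Protocol article*

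**What the plan says.** Protocol article, section {11b} on discontinuing or modifying the allocated intervention, gives the reasons for stopping: "Patients will discontinue NIV treatments in case of improvement, worsening leading to intubation, or in case of death".

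Statistical methods {20a}: the raw sore risk at each time point has as its denominator the patients on NIV at that time. A patient on a planned break still counts; a patient weaned off does not. The modified ITT analysis excludes patients with under 12 h of NIV and makes no distinction by reason.

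Outcomes {12}: the outcomes are sores (onset, number, stage, location), comfort, eye irritation, adherence, vasoactive drugs and costs. On stopping, the section says "The study will also monitor the number of patients that interrupts NIV due to discomfort". Intubation and death are not listed.

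Plans for assessment and collection of outcomes {18a}: the variables include NIV interruption, daily NIV duration and discharge status. Intubation is not named.

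Interim analyses {21b}: one look at two-thirds of the sample, with two-sided p < 0.01 on sore incidence as the only criterion. The section on the data monitoring committee {21a} nevertheless asks that group "to be involved in the safety monitoring interim analysis".

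Adverse event reporting and harms {22}: "Possible minor adverse events consequent to the use of noninvasive ventilation interfaces consist of pressure sores, dryness of the mouth, eye redness, and discomfort". It says that all of these are recorded and reported as outcomes.

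**The concern.** The patients enrolled are those in whom NIV is meant to avoid, replace or shorten invasive ventilation. The Abstract motivates the trial by saying that sores harm comfort and tolerance, "often leading to NIV failure and adverse outcomes", and the Background reports that "NIV failure is observed in 8% of hypercapnic" patients.

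Both the on-NIV denominator and the 12 h exclusion condition on something that happens after randomisation and that the allocated strategy might affect. If the arms differ in NIV failure, and the patients who fail are also those more prone to sores, the arm with more failures shows a lower sore risk among those remaining. Nothing in the described analyses would reveal this, because NIV failure is not compared. For the same reason, a favourable difference in NIV failure would also go unreported.

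**Working it through.** **1. The plan's own figure.** Sample size {14} starts from "Given a type I error of 0.05, a power of 0.8", a control risk of 23%, a 10-point difference (read as 23% v 13%) and 5% dropout. With unpooled variance and a two-sided test (sidedness is not stated there):

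n = (0.23×0.77 + 0.13×0.87) × (1.960 + 0.842)² / 0.10² = 227.8.

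227.8 × 1.05 = 239.2 and 227.8 / 0.95 = 239.8, so 239 per group is reproduced. The sample size is not at issue.

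**2. How many failures to expect.** The Background's 8% serves as a proxy for intubation or death on NIV. 0.08 × 239 ≈ 19 per arm, and 0.08 × 478 ≈ 38 in all. At the interim, two-thirds of 239 ≈ 159 per arm, and 0.08 × 159 ≈ 13.

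**3. What a comparison by arm could show.** With 8% in both arms, the 95% CI half-width is:
- end: 1.96 × √(2×0.08×0.92/239) = 4.9 points
- interim: 1.96 × √(2×0.08×0.92/159) = 6.0 points

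Power (two-sided 0.05, pooled variance under the null) against a control rate of 8%:

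| Rotation-arm rate (assumed) | 239 per arm | 159 per arm |
|---|---|---|
| 12% | 31% | 22% |
| 14% | 55% | 40% |
| 16% | 77% | 59% |
| 18% | 90% | 76% |

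The comparison is feasible, but it reliably detects only about a doubling.

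**4. Possible bias in the on-NIV sore risk.** Assume no true effect (sore risk 23% in both arms), a fraction r removed by intubation or death, and a sore risk q among those removed. The risk seen among those still on NIV is (0.23 − r×q)/(1 − r). Take r = 8% (control) and 16% (rotation), with all removals before 36 h:

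- q = 23% (unrelated): 23.0% v 23.0%, difference 0
- q = 46% (twice): 0.1932/0.92 = 21.0% v 0.1564/0.84 = 18.6%, difference 2.4 points
- q = 69% (three times): 0.1748/0.92 = 19.0% v 0.1196/0.84 = 14.2%, difference 4.8 points

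With r equal in both arms the difference is 0 for every q. With r = 8% v 12% it is 1.1 points (twice) and 2.3 points (three times).

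**5. Against the significance threshold.** At 239 per arm and an average risk near 18%, p < 0.05 needs 1.96 × √(2×0.18×0.82/239) = 6.9 points. With the reduced on-NIV numbers (239×0.92 ≈ 220 and 239×0.84 ≈ 201) it is slightly more. The standard error is then 3.9 points at the pooled risk of 19.9% (twice) and 3.6 points at 16.7% (three times). The chance of a significant result favouring rotation when there is no effect is P(Z > 1.96 − 2.4/3.9) ≈ 9% and P(Z > 1.96 − 4.8/3.6) ≈ 26%, instead of 2.5%.

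**6. Simply counting removed patients as sore-free does not cure this.** In the same scenario the spurious benefit is 8 points × q = 1.8, 3.7 or 5.5 points for q = 23%, 46% or 69%.

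**The case against.** A reader might make four stronger inferences, and the documents support none of them.

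- *Sore follow-up ends with NIV.* Section {11b} ends treatment only. Participant timeline {13} plans skin checks every 12 h for four days, with no stop when NIV ends. The primary outcome in {12} carries no on-NIV condition, and the analysis is declared ITT. The loss comes from the denominator and the 12 h exclusion in {20a}.
- *The trial cannot see harm.* Discharge status is collected {18a} and is to be evaluated {13}, so in-hospital deaths should be obtainable. Interruption for discomfort, discomfort score, eye irritation and daily NIV duration are also followed. But a patient who is intubated and discharged alive would not be identified by discharge status, and no comparison by arm is described for either event.
- *Six-hourly rotation is harmful, or the trial claims to reduce NIV failure.* The Background calls rotation feasible in hypercapnic adults and generally accepted as improving tolerance. The harms section gives reasons for thinking serious events remote. The stated objective is sores alone.
- *A doubling of failure would by itself produce a false win.* The expected bias stays below the roughly 7 points needed for significance. It would raise the chance of a false win without making one likely.

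It can also be said that safety tables and the committee's material belong to a full protocol, analysis plan or charter not shown. That is fair for tables, and the committee section does not confine that group to the sore p-value. It is less persuasive for the outcome list, the denominator and the interim criterion, which this document fixes, or for the list of recorded variables: intubation cannot be reliably analysed later if no field captures it.

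**Conclusion.** The point holds in a limited form. Intubation and death end NIV and remove patients from the on-NIV sore risk, and early failures also leave the modified ITT set. Neither event is a listed outcome, intubation is not a named variable, and the stated interim criterion contains no safety endpoint. Intubation is the clearer gap.

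The possible distortion is about 2 to 5 points, against a design difference of 10. This rests on assumptions that the documents do not supply: failure doubling from 8% to 16%, all of it before 36 h, and removed patients carrying two to three times the average sore risk. Later failures would give less at 36 h, and equal or unrelated removal gives none. It is a gap in what the trial would be able to show, and a cheap one to close.

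Separately and of minor weight, {22} says that mouth dryness is recorded and reported as an outcome, but it appears in neither {12} nor {18a}.

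**What to change.** 1. Add the reason for stopping NIV to the 12-hourly sheets, using the three reasons already in {11b}.
2. Report NIV failure (intubation or death) by 96 h, and in-hospital death, by allocated arm in all randomised patients, as a difference with 95% CI. Do so at the end of the trial and, for the monitoring committee, at the interim.
3. Analyse the 36 h primary outcome in all randomised patients instead of relying on the on-NIV denominator, and state in advance how intubation and death before 36 h are handled. The skin checks already planned for four days can supply sore status after NIV stops. Since counting removed patients as sore-free can also bias the result, add a sensitivity analysis under a different handling.
4. Reconcile the mouth-dryness statement in {22} with {12} and {18a}: add the field or drop the statement.

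Cost: one field taken from the medical record (two if mouth dryness is kept) and one table, with no extra visit or patient. Precision is limited, at about ±4.9 points with 8% failure and 239 per arm and about 77% power for 8% v 16%, so the estimate and its interval should be reported and a non-significant difference should not be read as reassurance.
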